As such, this study included 2 main groups of participants:QF2011 women enrolled in M@NGO (n = 108, including 1 intrauterine death). These participants were enrolled in both M@NGO and QF2011. Some were already M@NGO study participants at the time of the floods and where subsequently recruited to QF2011; others were pregnant at the time of the floods and were recruited into both studies simultaneously. At recruitment to the QF2011 study, M@NGO women may still have been pregnant or they may have already given birth as the inclusion criteria stated only that they must have been pregnant on January 10, 2011.QF2011 women not enrolled in M@NGO (n = 122). This group included women who had declined participation, did not meet the selection criteria for the M@NGO study, or who were recruited after the close of M@NGO (May 31, 2011).

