A number of women were recruited into QF2011 more than 10 months after the floods (n = ~50). Given that a 12-month post-flood questionnaire was planned, which repeated the administration of the recruitment questionnaire, the steering committee chose to send these women a single questionnaire at 12 months post flood rather than have them repeat the same questionnaire 2 months apart. As such, these women lacked a “recruitment IES-R” score. In order to impute these missing values, multiple regression was used to estimate their recruitment IES-R scores from post flood questionnaire responses. We used the dataset of women who had completed both the recruitment and the 12-month post flood questionnaires, and created separate algorithms for each IES-R sub-scale (Intrusions, Avoidance and Hyperarousal). Using this set of complete data, we regressed each recruitment IES-R sub-scale score on 12-month post-flood IES-R sub-scale scores, and other related scores that maximized the variance explained (STAI, PDI, PDEQ, MHC, etc.). The models explained 35.5 % (Avoidance), 44.2 % (Intrusions), and 49.1 % (Hyperarousal) of the variance in the recruitment scores. The regression coefficients from these results were used to create the equations we used for imputing the missing IES-R sub-scale scores for women who had not completed a Recruitment questionnaire. Once the sub-scales had been successfully imputed, IES-R Total scores were computed as usual by summing the sub-scales.

Maternal psychological health, psychosocial factors and other maternal measures

*Maternal anxiety (recruitment, 12 months post-flood, 6-12 weeks, 6 months, and 2½ years)*

The State-Trait Anxiety Inventory (STAI; [97]) is a valid and reliable self-report measure of how one generally feels (trait) or currently feels (state). We administered the State scale of the STAI at recruitment, 12 months post flood, and at 6-12 weeks and 6 months. At 2½ years we administered the Trait scale of the STAI. Each scale has 20 items and participants are asked to rate statements (e.g., “I am happy” and “I lack self-confidence”) on a 4-point Likert scale (rated from Almost Never to Almost Always).

*Depression (6-12 weeks and 6 months postpartum)*

As noted in the M@NGO protocol section, the EPDS (Edinburgh Postpartum Depression Scale) was administered as part of M@NGO to assess maternal depression in pregnancy and again at 6-12 weeks and 6 months postpartum.

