##### Maternal short-term response to the floods

Our first task is to understand the associations among the psychosocial and biological responses of the mother to the stress of the flood. Associations among objective stress (QFOSS), cognitive appraisal, peritraumatic distress (PDI) and dissociation (PDEQ), PTSD symptoms (IES-R), and maternal diurnal cortisol will be explored using correlations, and trend analyses to determine if any of the associations are non-linear. We will also test the ability of maternal genes associated with the HPA axis to moderate the effects of flood stress on maternal diurnal cortisol after the floods.

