##### Maternal mental health

Next, we will examine genetic and psychosocial mediators and moderators of the associations between flood stress and 12-month post-flood maternal outcomes such as symptoms of anxiety (STAI) and PTSD, as well as positive mental health (MHC-SF). We will test the ability of maternal coping style (Brief COPE) and specific candidate genes to moderate the effects of objective stress exposure on mental health outcomes. For women who had the EPDS administered before the floods, we will also determine the moderating effects of pre-flood depression (as measured by the EPDS) in the association between objective stress exposure and maternal mental health outcomes. Our general approach is to use hierarchical multiple linear regression, adding variables into the equation one block at a time. We first regress maternal mental health on exogenous variables such as maternal genotype and demographics; next, we add objective stress exposure; peritraumatic distress and dissociation; then psychosocial variables needed for the interaction (e.g., coping style); and finally we test one interaction at a time (e.g., objective stress-by-coping). We also test moderation and mediation effects directly using the SPSS PROCESS command; the mediation analyses include bootstrapping.

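### Recruitment IES-R for about 50 of 230 women is a single regression prediction with no residual draw described, then related to PDI and PDEQ, which were among the predictors

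*Protocol article*

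**What the plan says.** The protocol article, under Subjective, enduring distress from the flood, explains why the score is missing: "A number of women were recruited into QF2011 more than 10 months after the floods (n = ~50"), and "the steering committee chose to send these women a single questionnaire at 12 months post flood". These women therefore have no recruitment IES-R.

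The same section gives the remedy used. In women with both questionnaires, "we regressed each recruitment IES-R sub-scale score on 12-month post-flood IES-R sub-scale scores, and other related scores that maximized the variance explained". The related scores are listed as STAI, PDI, PDEQ and MHC, and the list is left open. The models explained 35.5% (Avoidance), 44.2% (Intrusions) and 49.1% (Hyperarousal) of the variance in the recruitment scores. Then "The regression coefficients from these results were used to create the equations we used for imputing the missing IES-R sub-scale scores", and the total was formed by adding the sub-scales in the normal way. The text describes no residual term, repeated imputation, or comparison without these women.

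Under Maternal short-term response to the floods the article plans: "Associations among objective stress (QFOSS), cognitive appraisal, peritraumatic distress (PDI) and dissociation (PDEQ), PTSD symptoms (IES-R), and maternal diurnal cortisol will be explored using correlations". The opening of Data analysis and power states the model behind this: peritraumatic responses predict PTSD symptoms.

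**The concern.** A value read off a fitted regression equation has no scatter around that equation. Two things follow for the imputed women.

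- **Compressed spread.** Their scores vary only as much as the predictors can explain, which here is half or less of the real variance.
- **Built-in association.** Their scores lie exactly on the plane defined by the predictors. When IES-R is related to one of those predictors, these women show the fitted relationship by construction and add no evidence for it.

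The overlap is direct for PDI and PDEQ. Women who received only the 12-month questionnaire have only 12-month PDI and PDEQ. If they are included in the correlations, those are the same post-flood responses that were available to the imputation equations. Part of the explanatory model under test is then written into the data. Subjective distress is also one of the components named in the primary research question, so the score is used widely.

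**Working it through.** **Inputs from the protocol article**
- Cohort (Participants): "QF2011 women enrolled in M@NGO (n = 108, including 1 intrauterine death") and "QF2011 women not enrolled in M@NGO (n = 122"). N = 108 + 122 = 230.
- Imputed women: m = about 50. Share = 50/230 = 21.7% (45 to 55 women gives 19.6% to 23.9%).
- Women with an observed score, if everyone else has one: 230 − 50 = 180.
- R² of the imputation models: 0.355, 0.442, 0.491. These need individual data and cannot be reproduced, so they are taken as given.

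**Step 1: spread of the imputed sub-scales.** A prediction without a residual has variance R² times the true variance, so its SD ratio is √R².
- Avoidance: √0.355 = 0.60
- Intrusions: √0.442 = 0.66
- Hyperarousal: √0.491 = 0.70

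**Step 2: pooled sample.** Relative variance v = ((N − m) + m·R²)/N. The covariance with a predictor is preserved, so its correlation is multiplied by 1/√v, and R² on the predictors becomes R²/v. This takes means and relationships to be the same in both groups, and the predictor to be the same measure throughout.

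| Sub-scale | v | 1/√v | R² before | R² pooled |
|---|---|---|---|---|
| Avoidance | (180 + 17.75)/230 = 0.860 | 1.078 | 0.355 | 0.413 |
| Intrusions | (180 + 22.10)/230 = 0.879 | 1.067 | 0.442 | 0.503 |
| Hyperarousal | (180 + 24.55)/230 = 0.889 | 1.060 | 0.491 | 0.552 |

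With 45 imputed women the inflation factors are 1.070, 1.060 and 1.054. With 55 they are 1.087, 1.074 and 1.067.

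**Step 3: error rate of a partial test.** Suppose IES-R is regressed on its own imputation predictors. The imputed women have zero residuals, so coefficients and residual sum of squares stay as in the 180 observed women. Only n and the degrees of freedom rise. With six predictors (an assumption, since the list is open) the reported standard error shrinks by about √(180/230) × √(173/223) = 0.885 × 0.881 = 0.78. The nominal 5% boundary of 1.96 then corresponds to 1.96 × 0.78 = 1.53 true standard errors, which is exceeded by chance in about 13% of studies.

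**Step 4: simulation.** N = 230, 50 imputed, six predictors with pairwise correlation 0.4, normal data, missing at random. All of these except the two counts are assumptions.

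| Quantity (Avoidance / Intrusions / Hyperarousal) | Complete data | As in the article | Residual draw added |
|---|---|---|---|
| R² on the predictors | 0.370 / 0.456 / 0.503 | 0.433 / 0.521 / 0.567 | 0.377 / 0.461 / 0.508 |
| Correlation with one predictor | 0.42 / 0.47 / 0.50 | 0.45 / 0.50 / 0.52 | 0.42 / 0.47 / 0.49 |
| False positives, nominal 5% | 5.3% / 4.9% / 5.7% | 13.1% / 13.0% / 14.4% | not run |

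Within the imputed women R² is 1.00. The simulation agrees with steps 2 and 3, and a residual draw returns R² and the correlation to about the complete-data level.

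**The case against.** **The effect on the planned correlations is modest.** This stands. The short-term response section plans correlations and trend analyses, where the inflation is about 6 to 8%. The 13% figure belongs to a joint regression on the imputation predictors, which the explanatory model invites but that section does not spell out.

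**The IES-R occasion is not named.** This also stands. The short-term heading points to the recruitment score, and the finding rests on that reading.

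**The predictor list is open.** The article does not say which scales entered which of the three equations, so the exact dependence holds for whichever scales were used. PDI and PDEQ are named in the list.

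**Most outcomes lie outside the equations.** This stands. QFOSS, cortisol, placental and child measures are not named as predictors. For an outcome unrelated to the predictors given IES-R, simulated slopes and standard errors were acceptable.

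**An unseen analysis plan may deal with it.** It may add a sensitivity analysis. But the article reports this imputation as already done, so the criticism is of a stated method and not of a missing detail.

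A reader might infer three stronger points that the article does not support:

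- **The 12-month mental health models are circular too.** Their outcomes are "12-month post-flood maternal outcomes such as symptoms of anxiety (STAI) and PTSD, as well as positive mental health (MHC-SF"), and these scales overlap with the imputation predictors. But the regression blocks under Maternal mental health are exogenous variables, objective stress, peritraumatic distress and dissociation, psychosocial variables and one interaction. Recruitment IES-R is not listed, so the problem arises there only if it is used as a predictor.
- **Screening cut-offs will under-count cases.** The cut-offs of 22, 25 and 33 are cited as published suggestions, and no analysis described applies them.
- **The imputed score is really postnatal mood.** Women recruited more than 10 months after the flood had already given birth, so a measured recruitment score would have been postnatal as well. Imputation did not cause this and better imputation would not remove it. The article openly allows recruitment after birth, and the IES-R asks about symptoms related to the floods.

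**Conclusion.** The concern holds in a limited form. The recruitment IES-R sub-scales of about 22% of the cohort are deterministic predictions from three regressions and are treated as observed. They have 0.60 to 0.70 of the true SD and are exact functions of scales that IES-R is then related to, explicitly PDI and PDEQ. In the pooled sample, correlations with those scales are inflated by about 6 to 8%, and R² on the predictors rises from 0.355, 0.442 and 0.491 to about 0.41, 0.50 and 0.55. A partial test at nominal 5% runs at about 13%.

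This assumes that the short-term response analysis uses the recruitment score, that all 230 women are analysed with the remaining 180 observed, that missingness is at random, that no residual was added (the text mentions only coefficients) and, for the error rate, that there were six predictors. It should be fixed because the harm falls on a named link in the explanatory model and the repair uses data already held. It does not call into question analyses of outcomes outside the imputation equations to the same degree.

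**What to change.** Replace the single predicted values with multiple imputation that draws both residuals and regression parameters, and include the outcome of the analysis and any tested interaction in the imputation model. In the structural equation models, full-information maximum likelihood does the same job.

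For every analysis that relates recruitment IES-R to PDI, PDEQ or any other scale used in the imputation equations, report the observed-only result (about 180 women) alongside. State which scales entered each equation and which IES-R occasion the short-term response analysis uses. If cut-offs are ever applied, do not apply them to single imputed scores.

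The cost is an analysis re-run, a change of wording and some wider intervals. No new data are needed.

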##### Social support (16 months, 2½ years, and 4 years)

The six-item Social Support Questionnaire (Short Form) (SSQSF; [110]) seeks not only information about the support available to mothers in various situations, but also their level of satisfaction with the support available. This is crucial as perceptions of social support may be just as important as the actual receipt of same [111]. Part 1 asks the respondent to list all of the people who fit the description of the question, while part 2 asks how satisfied they are, in general, with the support provided by these people. The SSQSF has high internal reliability and correlates highly with the longer version of this tool [110].

##### Parenting stress (6 and 16 months, and 2½ years)

The Parenting Stress Index: Short Form (PSI; [112, 113]) contains 36 items with statements regarding parenthood (e.g., “my child smiles at me less than I expected”) for which mothers report their level of agreement on a 5-point scale from “strongly agree” to “strongly disagree”.

##### Parental handedness (16 months)

Because left or mixed handedness in the child may reflect neurodevelopmental insult [114, 115], we also assessed parental handedness as a control variable. In the Parental Handedness Questionnaire [116] mothers were asked to indicate which hand they use for a list of 11 activities, including writing, drawing, and throwing a ball. They were also asked to indicate if they knew which hand the child’s biological father used for the same activities.

##### Maternal Theory of Mind (TOM) (2½ years)

TOM refers to the understanding that other people have mental states (e.g., beliefs, understanding, intentions, desires, and emotions) that may differ from one’s own. Poor TOM is a common trait of autism. To control for parental TOM when examining associations between PNMS and TOM in the children, parental TOM will be assessed using the Empathy Quotient (EQ [117]). The EQ is a list of 60 statements about how easily the participant understands other people's feelings and how strongly they are affected by other people's feelings (e.g., “I often find it difficult to judge if something is rude or polite"). The statements are rated on a 4-point scale from ‘strongly agree’ to ‘strongly disagree’.

##### Partner Relationship (4 years)

The Relationship Quality Index is a 6-item scale that asks respondents to rate on a 7-point Likert scale, their level of satisfaction in various areas of their relationship (i.e. stability, strength, etc.). Response options range from 1 “very strongly disagree” to 7 “very strongly agree” for the first five items. Item six relates to the overall level of happiness in the relationship, and is scored from 1 “unhappy” to 10 “perfectly happy” [118]. The overall score is computed by taking the sum of all six items, with higher scores representing greater satisfaction within the partner relationship.

##### Parenting and family adjustment (4 years)

The 40-item self-report Parenting and Family Adjustment Scale (PAFAS) assesses parent and family adjustment, as well as parenting practices. The Parenting Scale is comprised of two domains: parenting practices (17 items) and parent-child relationship (11 items); while the Family Adjustment Scale is comprised of three domains: parental emotional maladjustment (5 items), family relationships (4 items), and parental teamwork (3 items) [119]. Respondents are instructed to rate each statement on a scale from 0 “not at all” to 3 “very much (most of the time)”, with respect to the past four weeks. The measure is scored by taking the sum of all items, some of which are reverse coded. The Family Adjustment Scale has been found to have good internal consistency and satisfactory construct and predictive validity [120].

#### Maternal-rated scales of child development

*Infant temperament (6-12 weeks, 6 months, 16 months, 2½ years, and 4 years)*

The Short Temperament Scale for Infants (STSI) was developed as part of the ‘Australian Temperament Project: A Series of Studies of Australian Temperament, Development and Behavior in Australian Children’ [121]. The STSI is a 30-item questionnaire in which parents rate the occurrence of common infant behaviors on a 6-point scale ranging from 1 (almost never) to 6 (almost always). The items yield five scales which measure the temperament dimensions of approach-withdrawal, rhythmicity, cooperation-manageability, activity-reactivity, and irritability. An overall “easy/difficult” score is calculated as the mean of the approach-avoidance, cooperation-manageability, and irritability scales. Infants scoring one standard deviation above and below the normative mean are classified as “difficult” and “easy” respectively. The STSI was administered to mothers at 6-12 weeks and 6 months. The companion Short Temperament Scale for Toddlers (STST; [122]) was administered at 16 months and 2½ years, and we will administer the version for older children, the Short Temperament Scale for Children (STSC; [122]), at 4 years.

##### Developmental milestones (6-12 weeks, 6 months, 16 months, 2½ years, and 4 years)

Mothers have been completing the appropriate age-range versions of the Ages and Stages Questionnaire (ASQ-3; [123]) at every assessment: at 6-12 weeks postpartum, the 2-month version was used; at every other age, precise, age-appropriate versions were administered. The ASQ-3 is a 30-item parent-rated questionnaire that assesses five domains of development: communication, gross motor, fine motor, problem solving, and personal-social. Parents complete the questionnaire by answering each item using a 3-point Likert scale: 'Yes', 'Sometimes', or 'Not Yet'.

*Language abilities (16 months and 2½ years)*

Language development was assessed using the short form of the MacArthur-Bates Communicative Development Inventory: Words and Sentences (MCDI; [124]) at 16 months. The mother was given a list of 100 words and asked to indicate whether her child “understands” (receptive vocabulary) or “says” (productive vocabulary) each word. At 2*½* years an age-appropriate version of the MCDI-III was used that contains 100 words to assess the child’s productive vocabulary; the scale asks additional questions about how the child combines words into sentences and how they use language to ask questions, and about mean utterance length. This maternal report helps to avoid situational and temperamental factors that can affect children’s performance at face-to-face assessments, such as lack of interest or cooperation in the tasks, perhaps due to illness and/or anxiety [125].

*Infant handedness (16 months, 2½ years, and 4 years)*

Following procedures described by Glover et al. [116] we ask mothers which hand their child usually uses for the following five activities: drawing or coloring, throwing a ball, hitting things, stacking blocks, and using a spoon.

*Social-emotional development (16 months)*

The Brief Infant-Toddler Social Emotional Assessment (BITSEA; [126]) is a 42-item questionnaire that aims to identify children at risk for, or currently experiencing, social-emotional/behavioral problems and/or delays in social-emotional competence. It addresses four domains: Externalizing, Internalizing, Dysregulation, and Competence. This tool allows mothers to provide information about how their children behave in different situations.

##### Childhood Anxiety (4 years)

The 34-item Spence Childhood Anxiety Scale (SCAS) scale for preschoolers [127] provides information on children’s anxiety-like symptoms. For the first 28-items, parents report on the frequency at which an item is true for their child: 1 (not at all) to 5 (very often true). Item 29 is an open-ended question about whether their child has experienced a traumatic event. Items 30-35 relate to whether the child has exhibited post-traumatic symptoms following the traumatic event, and are not scored. The 28 items provide an overall measure of anxiety, as well as data on six childhood anxiety sub-scales: generalized anxiety, social anxiety, obsessive compulsive disorder, physical injury fear, and separation anxiety.

##### Autism spectrum traits (2½ and 4 years)

The 15-item Autism Spectrum Rating Scales (ASRS; [128]) was designed to effectively identify symptoms, behaviors, and associated features of Autism Spectrum Disorders (ASD) in children and adolescents aged 2 to 18 years. Using a 5-point scale mothers indicate how often they observe their child engaging in specific behaviors. Sub-scale scores for Social/Communication, Unusual Behaviors, Peer Socialization, Adult Socialization, Atypical language, and Stereotypy can be calculated.

##### Asthma and allergies (4 years)

In order to investigate the role of PNMS in influencing the children’s developing immune system, mothers will complete a 16-item questionnaire pertaining to their own symptoms of asthma, eczema and allergies, and those of their child and partner. The questionnaire was adapted from the International Study of Asthma and Allergies in Childhood (ISAAC) questionnaire [129, 130].

